### Setting/ participants

The study will take place in primary care practices in a geographically and socially diverse sub-region of central England (Coventry, Warwickshire, Worcestershire, and Herefordshire PCTs).

#### Practice Nurses/ Health Care Assistants

PNs/ HCAs in both the intervention and control arms will deliver sessions within the practices in which they are employed, to registered patients. All PNs/ HCAs who are randomised to the intervention group will be trained by the research team, and demonstrate competence to deliver the intervention, as assessed by the research team (details provided below) before delivering the intervention to patient participants. All PN/ HCAs randomised to the control group will be provided with one to one training on the control intervention and trial procedures from a member of the research team, usually involving one visit to their practice of approximately one hour. The PN/HCAs in the control arm will be offered the opportunity to receive training in the self-efficacy plus planning intervention after all participating patients from their practices have completed the 6 month follow-up measures.

#### Patients

To be eligible for inclusion in the trial, potential participants must be patients in a participating practice, as well as:

a) be aged between 16 and 65 years old,

b) have one of the following chronic conditions where physical activity has been shown to have a positive effect on health status [1]: hypertension, type 2 diabetes, pre-diabetes (impaired glucose tolerance, insulin resistance), low back pain, fibromyalgia, coronary heart disease, cardio-vascular disease, hypercholesterolemia, osteoporosis and osteoarthritis, or are overweight or obese,

c) not currently being investigated/treated by secondary care specialists for the condition (s) or are awaiting investigation/treatment by secondary care specialists for the condition (s),

d) are "sedentary" in terms of not meeting the 30 mins/day at least 5 times/ week guidelines [1],

e) are able to speak English (and therefore could potentially benefit from the PN/ HCA intervention session). This is because the intervention is to be delivered and interpreted verbally and there are not sufficient resources to employ interpreters. Where participants cannot adequately read English, the PN/HCA will read the patient information sheet, consent form and worksheet instructions.

f) do not have learning difficulties that would preclude active engagement with the intervention session,

g) do not have mental health problems i.e. anxiety, depression that would preclude active engagement with the intervention session, or where the patient is being investigated/treated by secondary care specialists for the problem,

h) wish to participate,

i) receive a letter of invitation to the study from their practice.

### Study intervention

#### Self-regulation intervention

Participants will receive the intervention in two face-to-face sessions, one week apart, with a telephone or face to face follow-up two weeks after the second session. The choice of face to face or telephone follow up will be decided by the PN/HCA in consultation with the patient, and will be dependent on the patient's and PN/HCA's own preference. Each session may be up to 30 minutes in duration, although it is anticipated that the follow-up session will be shorter. The intervention is fully detailed in the intervention manual, a copy of which is available on request from the first author.

Session one consists of motivational techniques to increase the patients' self-efficacy [16] about their ability to increase their walking, by requiring them to rehearse previous instances where they have successfully managed to complete long walks, or where they found such walks easy [27]. It also includes volitional techniques to facilitate realistic goal setting [28], and to translate intentions into practice (e.g. action plans) [17,20]. Session two consists of a review of progress since session one, involving positive feedback in relation to effort and achievement, and possible revision of goals set and action plans. It also includes the volitional technique of supportive/ facilitative planning, whereby the participant is encouraged to identify what factors support increased walking, and make plans to bring about those factors [14]. In this sense, it is similar to coping planning [17], but with a focus on how to increase and strengthen helpful factors, rather than how to overcome barriers. The follow-up session consists of an abbreviated version of some of the same techniques delivered in session two.

#### Training and fidelity assurance of self-regulation intervention

Each walking intervention PN/ HCA will be trained using the training manual and materials that have been developed, and refined in earlier phases of this research. All PN/HCAs will complete two training sessions, totalling seven hours. Training will involve formal presentations to introduce the PN/HCAs to the theory and research underpinning the intervention and the essential elements of the intervention: participative learning, practising delivery of intervention techniques, observation, feedback, discussion and homework. All PN/HCAs will become familiar with the intervention manual and materials. The training sessions will be conducted one week apart to allow PN/HCAs to absorb and reflect on what they have learnt and to re-read through the intervention materials.

After participating in the training sessions, PN/HCAs will be observed delivering both intervention sessions to either a colleague or acquaintance of the PN/HCA, or a researcher/ administration officer from Coventry University. Their competences will be assessed using 20-point checklists of intervention behaviours, rated by a member of the study team. To be certified competent in delivering the intervention, PN/HCAs need to achieve a minimum score of 15 out of a possible score of 20 for both sessions. PNs/HCAs will only deliver the intervention as part of the main trial after achieving this level of competence. Where the minimum level of competence is not achieved, the PN/HCA will be given feedback on potential areas for improvement and asked to repeat the assessment of competence on a later occasion. Irrespective of whether the minimum level is achieved, feedback on delivery will be given, with emphasis on where good performance has been achieved, as well as where improvement is possible, to both encourage and inform future delivery.

#### Information provision control intervention

The PN/HCA will give their patients an information pack of materials promoting walking produced by the British Heart Foundation and Walking the Way to Health. The PN/HCA will answer any questions the patient may have about walking more, and continue to provide usual care for that patient with regard to walking.

### Outcome measures

The main outcome measure will be mean daily number of minutes walked in the past week, assessed at all time points using the New Lifestyles NL-1000 Activity Monitor Pedometer (New-Lifestyles Inc, Lees Summit, Missouri, USA). This pedometer provides readings on number of minutes walked and step counts, over each of the previous seven days. The intensity threshold of each pedometer will be set to record movement on a setting of four or above (the range is 1 to 9), to assess physical activity of at least moderate intensity.

Psychological process will be assessed using one of two Theory of Planned Behaviour (TPB) [15] questionnaires, both of which measure several constructs. A longer 26-item version measures intentions, self efficacy/ PBC, attitudes, subjective norms, control beliefs and associated perceived power to inhibit/ facilitate behaviour in relation to walking for at least 30 minutes on average a day over the next 7 days [29]. A brief 6-item version of the questionnaire assesses only intentions, self efficacy/ PBC, attitudes, and subjective norms. Both versions of the TPB questionnaire are abbreviated versions of measures previously developed [10] and validated [13,14] in studies of walking with an adult volunteer general public sample.

Data on NHS resource use and personal costs to patients will be collected using standard measures for economic analysis [30]. Impact on Quality of Life will also be assessed using the EQ-5D questionnaire [31,32]. Comparing this with costs (directly and indirectly related to patient management) will enable incremental cost-effectiveness of the intervention to be estimated.

### Trial procedures

#### Practice recruitment

Practices in the relevant PCTs will be contacted by the study team, with the support of the local West Midlands (South) Primary Care Research Network (PCRN). Practices will be sent an invitation letter and short information sheet via the post, and this will be followed up by a telephone call. The research team will provide additional information to those practices that are interested, including a consent form for PN/HCAs, which provide a clear description of what is involved in participating in the trial. Practices will be randomised to the self-regulation intervention arm or to the information provision control arm. Randomisation will only proceed after the explicit agreement from the practice manager or a GP principal has been obtained, and the relevant PN/HCA has consented to delivering an intervention to 20 patients. Practices will be recruited on the understanding that if they are allocated to the control arm (which would still constitute good routine care), they will be offered training in the self-regulation intervention upon completion of study follow-ups.

#### Practice randomisation

Randomisation will be at the practice level, and will be stratified by practice size and index of deprivation scores, as assessed by practice postcode [33]. Strata will be defined according to whether the practices are above or below the median practice list size of 6127 for the four PCTs and whether the practice deprivation index is above or below the median deprivation index of 27.85, 14.57, 15.51 and 17.55 respectively for Coventry, Warwickshire, Worcestershire, and Herefordshire PCTs.

Randomisation will be performed by researchers at Coventry University external to the study team using materials prepared by the trial statistician ([name]). These researchers have four lists, one for each of the four stratified groups: (a) small practices + high deprivation, (b) small practices + low deprivation, (c) large practices + high deprivation, (d) large practices + low deprivation. Each list contains a random ordering of "intervention" and "control" allocations. When the study team receive a consent form from a PN/ HCA to confirm that their practice will enter into the trial, the appropriate list will be consulted by the researchers external to the study team, who will record the practice name, and indicate whether they are intervention or control.

#### Patient recruitment

An initial list of patients will be selected from practice computerised records, using electronic searches, to identify eligible patients. A list of a random subsample of eligible patients (initially 200) will be sent to the GP or PN in each practice who will be nominated as responsible for referring patients. They will be given the inclusion criteria to guide recruitment.

Identified patients will be sent an invitation letter addressed from the practice, which emphasises that the intervention is intended for people who do less than the recommended 30 minutes of moderate or vigorous physical activity on at least five days a week. They will also be sent a patient information sheet explaining the study. Patients who are interested in taking part will be required to call the practice to make their first appointment with the PN/HCA delivering the intervention. Contact details for further information about the study will be included on the invitation letter and information sheet. Where the initial post to 200 patients does not yield 20 participating patients, further mail-outs to another random sample of eligible patients will be made.

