#### Patient consent, receipt of intervention, and follow-up measurements

For both experimental conditions, each patient attends a face-to-face session at their own practice with the PN/HCA who is delivering the session. During this session, they are screened for whether they already do more than 30 minutes of moderate or vigorous physical activity per day on at least 5 days a week. If they are not already achieving this recommended level of physical activity, they are asked to provide informed consent, and complete the baseline (t1) questionnaire, which includes the full TPB measure, the EQ5D, and measures of ethnicity, employment status and education level. Information on patient date of birth, gender, and the clinical condition for which they were flagged (e.g. diabetes, hypertension, etc) will be recorded on a standardised form by PN/HCAs. The form will be sent to the research team, along with their contact details. Weight and height information for each patient will be recorded by the PN/HCA at baseline, which will allow calculation of body mass index. After this point, the procedure differs for patients in practices allocated to the self-regulation intervention condition, and patients in practices allocated to the information provision condition (see Figure 1).

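### Patients are checked, screened and consented by practice staff after their practice has been allocated, so selection can differ by arm, and a residual difference in pre-intervention walking cannot be directly checked or adjusted for as planned

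*Protocol article*

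**What the plan says.** **Allocation.** The Practice recruitment section sets two conditions: "Randomisation will only proceed after the explicit agreement from the practice manager or a GP principal has been obtained", and the PN/HCA has consented to deliver to 20 patients. Practice randomisation gives the trigger: "When the study team receive a consent form from a PN/ HCA to confirm that their practice will enter into the trial", external researchers consult the stratum list and record the arm. Neither section requires a patient list, or any patient's consent, to exist first.

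**Training.** "All PNs/ HCAs who are randomised to the intervention group will be trained by the research team, and demonstrate competence to deliver the intervention", and this happens before they see trial patients. Control PN/HCAs have their own shorter training. Each provider therefore knows the arm before meeting a trial patient.

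**Listing and referral.** "An initial list of patients will be selected from practice computerised records, using electronic searches, to identify eligible patients". Then "A list of a random subsample of eligible patients (initially 200) will be sent to the GP or PN in each practice"; that clinician is nominated as responsible for referral. "They will be given the inclusion criteria to guide recruitment". Patients are invited by letter and must telephone the practice themselves. Any further mail-out is again a random sample.

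**Screening and consent.** In both arms, "each patient attends a face-to-face session at their own practice with the PN/HCA who is delivering the session". Current activity is screened and consent is taken in that session, and the arm-specific procedure then follows.

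**Walking before the intervention.** Intervention patients wear a pedometer for a week before their first self-regulation session. Control patients receive their first pedometer after the information session, and that week is their first outcome.

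**Adjustment.** The Analysis section adjusts for practice size and deprivation, and for age, gender, BMI, ethnicity, employment status, education and clinical condition. Walking is not among the covariates.

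**The concern.** Randomising practices balances practices. It protects the comparison of patients only if the way patients enter does not depend on the arm. Here three steps lie with practice staff: the referral check, the activity screen and the consent discussion. The last two certainly take place with a provider who knows the allocation.

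The arms ask for very different commitments. A control patient attends one session and takes away a pack. An intervention patient attends an initial session, two recorded sessions of up to 30 minutes each and a follow-up. Who is referred, who is judged insufficiently active and who agrees could plausibly differ.

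The activity screen matters most. It asks about moderate or vigorous activity, and the primary outcome is minutes walked on a pedometer set to record at least moderate intensity. If the screen is applied more leniently in one arm, the outcome mean shifts directly. Such a shift adds to, or subtracts from, the estimated treatment effect, and the target difference is only 5 min/day.

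**Working it through.** **1. Reproduce the planned power.** Inputs from the Sample size section: 10 PN/HCAs per arm, 20 patients each, SD 15 min/day, ICC 0.010, difference 5 min/day, stated power 85%. The test level is not stated; two-sided 5% is assumed.

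- Design effect = 1 + (20 − 1) × 0.010 = 1.19
- Effective patients per arm = 200 / 1.19 = 168.07
- SE of the difference = 15 × √(2 / 168.07) = 1.636 min/day
- Power = Φ(5 / 1.636 − 1.96) = 86.3%

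This agrees with the stated 85% to within 2 points. A one-sided 5% test would give 92.1%, which does not agree, so the two-sided reading is kept.

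**2. Add a selection difference.** Let b be the between-arm difference in usual walking that remains after the planned covariates. The documents give no value, so b is assumed. The test statistic then shifts by b / SE.

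- Error rate with no true effect, b favouring the intervention: 1 − Φ(1.96 − b/SE) + Φ(−1.96 − b/SE)
- Power for a true 5 min/day, b against the intervention: Φ((5 − b)/SE − 1.96)

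| Assumed b (min/day) | b in SD units | Error rate (nominal 5%) | Power if b opposes the effect |
|---|---|---|---|
| 0 | 0 | 5.0% | 86.3% |
| 1 | 0.07 | 9.4% | 68.6% |
| 2 | 0.13 | 23.1% | 45.0% |
| 3 | 0.20 | 45.0% | 23.0% |

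**3. What the plan can and cannot detect.**

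- *Adjusted for:* age, gender, BMI, ethnicity, employment, education, condition, practice size and deprivation.
- *Comparable between arms though not in the model:* the full TPB questionnaire and EQ-5D at t1, collected in both arms.
- *Roughly comparable:* the first pedometer week in each arm, since both follow the same information pack and a chance to ask questions. The match is imperfect. Intervention patients are expecting further sessions, and their data are extracted by the PN/HCA, whereas control pedometers are posted to the research team. For the one-week comparison, the control week is itself the outcome and cannot serve as a baseline.
- *Not directly checkable or adjustable as planned:* a remaining difference in pre-intervention walking.

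**The case against.** The case on the other side has real substance.

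- **Listing is not by staff choice.** A reader might infer that practice staff pick the patients. The Patient recruitment section does not support that: an electronic search is followed by a random subsample, letters go out, and patients refer themselves. These are useful safeguards against hand-picking. They do not cover the referral check, the screen or the consent discussion.
- **The timing of the list is not stated.** A reader might take it as fixed that allocation precedes listing. That is only suggested by the order of the sections. What is clear is that nothing requires the list to come first, and that screening and consent come after allocation.
- **Much would be visible.** It is tempting to say that differential selection could be neither seen nor adjusted for. The measured covariates, the t1 questionnaires and the rough comparison of first pedometer weeks rule out so broad a claim. The gap is narrower: residual pre-intervention walking.
- **The size and direction are unknown.** The shifts in the table must persist after the covariates and among patients who all met one stated activity criterion. Nothing in the documents shows that they would, or which way they would run.
- **An article may omit procedure.** The exact date of each search and any masking of staff may be in the full protocol. The described sequence still has the delivering provider screening and consenting patients after training for a known arm.

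**Conclusion.** The point stands in a limited form. Recruitment after allocation, through staff who know the arm, is a real route to selection bias, and the plan has no common pre-intervention walking measure with which to check or correct it directly. The documents do not show that selection will differ.

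The illustration shows why small differences matter: 1 to 2 min/day, or 0.07 to 0.13 SD, would take the error rate to about 9% to 23%, or cut power from about 86% to between 69% and 45%. These figures rest on the protocol's SD and ICC, an assumed two-sided 5% test, a normal approximation, and assumed sizes of b net of the covariates. The problem is easier to prevent by ordering the steps than to repair in the analysis.

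**What to change.** 1. **Reorder.** After practice and PN/HCA consent, run the electronic search, draw the random list in mailing order including reserve batches, complete the GP or PN eligibility check, and freeze the list. Only then ask the external researchers for the allocation.
2. **Script the screen.** Use one fixed, scripted activity-screening question in both arms.
3. **Log the flow.** Record by arm the numbers invited, screened out and declining.
4. **Report.** Compare the t1 measures between arms and, as a rough check only, the first pedometer weeks.
5. **State the limit.** Step 1 closes the referral route only. Screening and consent still follow allocation, so the remaining risk should be declared as a limitation.

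The cost is a short delay before allocation and training, plus a simple log; no extra visits are needed. Closing the remaining route would take more: screening and consent before allocation is disclosed or by staff unaware of it, and the same pre-intervention pedometer week in both arms, used as a covariate. The sponsor should weigh that against the added burden on practices.

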#### Patient consent, receipt of intervention, and follow-up measurements

For both experimental conditions, each patient attends a face-to-face session at their own practice with the PN/HCA who is delivering the session. During this session, they are screened for whether they already do more than 30 minutes of moderate or vigorous physical activity per day on at least 5 days a week. If they are not already achieving this recommended level of physical activity, they are asked to provide informed consent, and complete the baseline (t1) questionnaire, which includes the full TPB measure, the EQ5D, and measures of ethnicity, employment status and education level. Information on patient date of birth, gender, and the clinical condition for which they were flagged (e.g. diabetes, hypertension, etc) will be recorded on a standardised form by PN/HCAs. The form will be sent to the research team, along with their contact details. Weight and height information for each patient will be recorded by the PN/HCA at baseline, which will allow calculation of body mass index. After this point, the procedure differs for patients in practices allocated to the self-regulation intervention condition, and patients in practices allocated to the information provision condition (see Figure 1).

**Figure 1 F1:**
[figure not shown]
**Flowchart showing planned study recruitment numbers, and timing of intervention sessions and measurements**.

For patients in practices allocated to the information provision control condition, the session will continue with delivery of the "information provision" intervention as described above: the PN/HCA will provide their patients with an information pack of materials promoting walking, and answer any questions the patient may have about walking more. At the end of this session, patients complete the post-intervention (t2) questionnaire, consisting of the brief TPB measure only, and are given a pedometer, with detailed instructions in its use. They are asked to wear it for a week, and return to the research team in a reply-paid envelope. This forms the first post-intervention assessment of walking.

For patients in practices allocated to the self-regulation intervention condition, the PN/HCA provides their patients with an information pack of materials promoting walking, and answers any questions the patient may have about walking more. Following this, two further face-to-face appointments will be booked, for delivery of the self-regulation intervention (as described above), at one week and two weeks after this initial session, plus the final intervention session four weeks after the initial session. At the end of this session, patients are given a pedometer, with detailed instructions for its use. They are asked to wear it for a week, and return it at their first intervention session where the PN/HCA will extract the data from the pedometer. This initial assessment of walking constitutes a pre-intervention measurement for those patients in the intervention arm.

Patients in practices allocated to the intervention condition then receive the self-regulation intervention, as detailed above. Sessions one and two will be tape-recorded, with the explicit agreement and signed consent of the patients involved. At the end of the second face-to-face session, patients complete the post-intervention (t2) questionnaire, and are given a pedometer, to wear for a week, and then return to the research team in a reply-paid envelope. This forms the first post-intervention assessment of walking.

Patients in practices allocated to the intervention condition receive a final follow-up intervention session, which may be by telephone or face-to-face, two weeks after their second face-to-face session. Despite this, the measurement procedures for patients in practices in both conditions are identical from t2 onwards.

At six weeks post intervention (i.e. six weeks after t2 for both groups), all patients are sent a questionnaire by post (t3) containing the brief TPB measure, and a pedometer, and asked to return these by post. At six months post intervention (t4), all patients are sent a questionnaire containing a full TPB measure, the EQ5D, and a final pedometer, which again they are asked to return by post.

To encourage retention, all participants who complete and return questionnaires or pedometers from t2 onwards will be sent postal feedback on their walking behaviour and psychological measurements in the form of a postal profile. Those who do not send back the pedometer at any measurement point will receive a reminder letter and follow-up telephone calls from the research team encouraging them to return these, as loss of numerous pedometers will be expensive, and threaten the validity of the study.

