### Analysis

Planned intention-to-treat comparisons of the two groups at one week, six weeks and six months post-intervention (i.e. six months after t2 for both groups) will be conducted, with the primary dependent variable being mean daily walking, as assessed by pedometer. Mixed effects linear models will be fitted to compare the groups with a random practice effect to allow for clustering. The models will adjust for baseline characteristics at both practice and individual level. The former will include practice size and deprivation index, and the latter will include age, gender, BMI, ethnicity, employment status, educational level and clinical condition leading to referral.

As indicated above, the primary response will be the mean daily walking distance observed over up to seven days. Where less than five minutes walking is recorded for any particular day, the reading for that day will be treated as missing, and not used in calculating mean daily duration of walking. When individual days' data are missing, so long as data are available for two or more days, the mean will be taken over these non-missing days. If no data, or data from fewer than two days, are available for a particular patient at a particular timepoint, that assessment of walking will be treated as missing. These missing values will be imputed based on the baseline characteristics of the practice and individual [34]. A secondary analyses will be conducted excluding patients with missing data.

Planned exploratory sub-group analyses will be conducted to determine if the intervention has larger or smaller effects for groups defined in terms of age, ethnicity, gender, socio-economic status, or clinical condition, to provide information on any adverse impacts on social inequality.

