#### Economic evaluation

Economic evaluation methods will, as far as possible, adhere to the recommendations of the NICE Reference Case [37]. The economic evaluation will consist of a within-trial analysis and economic modelling. Within trial analysis will compare direct costs and six month outcomes of patients randomised to intervention versus control. The perspective adopted will be that of the NHS and Public Social Services. A costing study will record intervention costs (to include staff time, capital, overheads and consumables), other NHS resource use (e.g. general practitioner visits) and patient expenditure. Unit costs for health care resources will be derived from local and national sources and performed in line with best practice [38]. Costs will be standardised to current prices where possible. Because of the short follow up period, we will not discount costs or benefits.

Comparison will be made between baseline and 6 months to estimate incremental cost-effectiveness ratios (ICERs) comparing the intervention with the control group in terms of the primary outcome measure (mean daily minutes walked in the past week) and costs [30]. Quality of life (EQ-5D) over the study period will be used to generate quality-adjusted life-years (QALYs) [39]. Outputs will be presented as ICERs, cost-effectiveness acceptability curves and expected net benefit. Sensitivity analyses will consider key cost drivers and factors that might affect the outcomes measured in order to explore uncertainty in the conclusions drawn.

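### The t2 pedometer is issued at consent in control but only after two further attended sessions in intervention, so non-attenders have no one-week reading, and the EQ-5D interval is about two weeks longer in intervention

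*Protocol article*

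**What the plan says.** All of this is in the Protocol article.

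- **Baseline (t1), both arms.** At the first visit, patients who pass screening consent and "complete the baseline (t1) questionnaire, which includes the full TPB measure, the EQ5D, and measures of ethnicity, employment status and education level" (Patient consent, receipt of intervention, and follow-up measurements).
- **t2, control.** It belongs to that same visit: "At the end of this session, patients complete the post-intervention (t2) questionnaire, consisting of the brief TPB measure only, and are given a pedometer" (text following Figure 1).
- **t2, intervention.** The self-regulation sessions are booked "at one week and two weeks after this initial session, plus the final intervention session four weeks after the initial session". The t2 measures come after the second of these: "At the end of the second face-to-face session, patients complete the post-intervention (t2) questionnaire, and are given a pedometer, to wear for a week".
- **Later measurements.** The t3 and t4 packs are posted to all patients, six weeks and six months after t2 in each arm. The Analysis section repeats the rule: "six months post-intervention (i.e. six months after t2 for both groups".
- **Analysis.** Group comparisons at one week, six weeks and six months are by intention to treat. Missing walking values are imputed from practice-level and patient-level baseline variables. A secondary analysis leaves out patients with missing data.
- **Economic evaluation.** "Within trial analysis will compare direct costs and six month outcomes of patients randomised to intervention versus control". EQ-5D is scheduled at t1 and t4 only. QALYs are to be generated over the study period, and the incremental ratios compare baseline with six months.

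**The concern.** The t2 clock starts at different distances from enrolment. A control patient cannot be lost between consenting and being handed the t2 pedometer, because both happen in one visit. An intervention patient must come back twice first. Patients who do not come back are likely to differ from those who do, and they have received less of the intervention. As described, no one-week reading is collected from them, and the article does not say when their six-week and six-month packs go out.

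The stakes are an upward error in the one-week effect if non-attenders benefit less than attenders. Separately, the health-economic comparison could credit one arm with quality-adjusted time merely because its two EQ-5D assessments lie further apart.

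**Working it through.** **1. The plan's own figure.** Inputs from Sample size: 200 patients per arm, 20 per PN/HCA, SD 15 min/day, intraclass correlation 0.010, difference 5 min/day. Two-sided 5% significance is assumed, as no level is stated.

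- Design effect = 1 + (20 − 1) × 0.010 = 1.19; effective n = 200 / 1.19 = 168.07 per arm.
- Standard error = 15 × √(2 / 168.07) = 1.636; 5 / 1.636 − 1.96 = 1.10; power = 86.3%.

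This agrees with the stated 85%. The power figure does not depend on the t2 clock and is not in dispute.

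**2. Timeline, in weeks from the initial session** (six months taken as 26 weeks).

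| | Control | Intervention |
|---|---|---|
| t1, first EQ-5D | 0 | 0 |
| t2 | 0 | 2 |
| Last scheduled intervention contact | 0 | 4 |
| t3 = t2 + 6 | 6 | 8 |
| t4 = t2 + 26, second EQ-5D | 26 | 28 |

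The intervention interval from t1 to t4 is longer by 2 / 26 = 7.7%. Week 2 for t2 is confirmed by the final session being placed both four weeks after the initial session and two weeks after the second self-regulation session.

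**3. One-week comparison.** The documents give no rate of missing session two, so a proportion d is assumed. Assume also that attenders gain 5 min/day over control, non-attenders gain nothing, and all controls return their pedometers.

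- True intention-to-treat effect = 5 × (1 − d).
- Excluding the missing, or imputing at the intervention-arm mean, gives 5.
- Imputing without regard to arm uses the overall observed mean, 5(1 − d) / (2 − d), so the estimate is 5(1 − d) + d × 5(1 − d) / (2 − d).

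At d = 15%: truth = 4.25. The arm-blind imputed value is 170 × 5 / 370 = 2.30, so the estimate is 4.25 + 0.15 × 2.30 = 4.59 (4.59 / 4.25 = 1.08, or +8%). Arm-mean imputation or exclusion gives 5 (5 / 4.25 = 1.18, or +18%).

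| Assumed d | True effect | Arm-blind imputation | Arm-mean imputation or exclusion |
|---|---|---|---|
| 5% | 4.75 | 4.87 | 5 |
| 15% | 4.25 | 4.59 | 5 |
| 30% | 3.50 | 4.12 | 5 |

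**4. QALYs.** If each arm is summed over its own t1 to t4 interval, the two extra weeks add utility × 2 / 52.18.

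- Utility 0.6 (assumed): 0.6 × 2 / 52.18 = 0.023.
- Utility 0.8 (assumed): 0.8 × 2 / 52.18 = 0.031, the same as a utility gain of 0.031 / 0.5 = 0.06 held for six months.
- Utility 0.9 (assumed): 0.9 × 2 / 52.18 = 0.034.

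**The case against.** The strongest reply is that the t2 clock is deliberate. The aims refer to follow-up for up to six months after the intervention, the trial is explanatory, and the article states twice that times run from t2 in both groups. That stands as a reason not to move everyone's clock. Counting from consent would simply give controls longer follow-up after their intervention. The alignment is imperfect, though: the final intervention session comes two weeks after t2, so t4 falls about 24 weeks after the last scheduled contact in intervention and 26 in control.

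A reader might infer several stronger things that the text does not support:

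- **That early dropouts leave the trial in one arm only.** They do not. The t3 and t4 packs go to all patients, the main analysis is by intention to treat with imputation, and only a secondary analysis excludes patients with missing data.
- **That the one-week comparison sets attenders against all controls.** Controls must also post the pedometer back, and the article provides reminders for non-return at any time point. Only loss before the device is issued is confined to intervention.
- **That the error is +18%, at every time point.** That figure needs the assumed 15%, zero gain and imputation at the intervention-arm mean. The article does not list arm among the imputation variables; without it the figure is about +8%. Non-attenders can still supply readings at six weeks and six months.
- **That QALYs and costs will certainly cover two extra weeks in intervention.** The Economic evaluation names a six-month horizon, and an analyst may scale both arms to it. For costs, no start date or recall period is given, so unequal cost periods cannot be shown.

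Session two is also booked at enrolment, so a scheduled date does exist, and Figure 1 is not available here. The article does not say that the scheduled date is the one used. An analysis plan could settle the dates and the economic period, but it cannot recover t2 readings that were never collected.

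**Conclusion.** The concern holds in a limited form. As described, t2 walking cannot be obtained from intervention patients who miss session two. Control has no equivalent step, and imputation from baseline variables carries no information on attendance. The direction is upward if non-attenders benefit less. The size is unknown: an overstatement of roughly 0.3 to 0.75 min/day (4.59 − 4.25 to 5 − 4.25) at an assumed 15%, against a target difference of 5, mainly at one week. At six weeks and six months the gap is an unstated follow-up date for these patients.

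The unequal EQ-5D interval, about 26 against 28 weeks, follows directly from the stated schedule. Its consequence of about 0.02 to 0.03 QALY per intervention patient depends on the assumed utility (0.6 to 0.9) and on QALYs being summed over each arm's own interval, which the text permits but does not state. Neither part affects the power calculation.

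**What to change.** 1. Post the t2 questionnaire and pedometer, on the scheduled session-two date, to any intervention patient who misses that session.
2. For those patients, count t3 and t4 from that scheduled date, and state this rule.
3. State that QALYs and costs are computed over one common period from the initial session in both arms, for example 26 weeks, interpolating utility between t1 and t4 in the intervention arm.

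The cost is a few extra postal packs, some wording, and a small scaling assumption about utility over the final two weeks. Re-anchoring t3 and t4 to consent for everyone is a trade-off against the stated post-intervention target and is not required.
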